### CVL processing

CVL specimens are tested for prostate-specific antigen (PSA), a marker for semen exposure, using the Abacus ABAcard® p30 test (Abacus Diagnostics, West Hill, CA); testing for CVL blood and leukocyte levels is also performed with Mutistix® 8SG urinalysis strips (Siemens Healthcare, Los Angeles, CA). CVL samples are centrifuged to separate into supernatant and cellular fractions; 8 mL of the CVL supernatant is collected, and aliquots are labeled and stored at -80 °C for subsequent assays. The remaining CVL supernatant is filtered through a 100 μm cell strainer, complete media is added, and the mixture is centrifuged and aspirated for supernatant. The pellet is resuspended in complete media, and from this, 3–4 million cells are used for multi-color flow cytometry staining via standard surface staining protocol (BD LSR Fortessa). The remaining cells are mixed with freezing media (10% dimethyl sulfoxide containing 90% human serum), and aliquots are stored in a liquid nitrogen freezer (-195 °C).

### Cervical cytobrush processing

Cytobrush samples are processed according to study procedures, then stained with trypan blue stain to check viability and cell count in the automatic cell counter (Invitrogen). The complete sample is used for real time flow cytometry staining.

### Cervical biopsy specimen processing

Biopsy samples are processed into a liquified cellular sample according to study procedures. A 10 mL volume of cells is mixed with trypan blue stain to check viability and cell count in the automatic cell counter. Remaining cells are used for real time multi-color flow cytometry immunophenotyping assay.

### Immune cell characterization

Staining of PBMC, CVL, cytobrush, and cervical biopsy samples is done at RT, while the cell counts for PBMCs, cervical biopsies, cytobrush cells, and CVL cells are done at 4 °C. Cytobrush (1–2 × 10^6^) and CVL (3–4 × 10^6^) cell suspensions are stained for 30 min in PBS containing 2% FBS (fluorescence-activated cell sorting [FACS] wash buffer: 1X PBS1000 mL, 2% FBS and 500 mg sodium azide). Cells are stained with fluorochrome-conjugated antibodies from BD Pharmingen or Biolegend (San Diego, CA) specific for CD3 (SP34-2), CD4 (OKT4), CD8 (RAP-T8), CCR5 (3A9), PD-1 (EH12.2H7), Ki-67 (B56), CD38 (HIT2), CCR7 (G043H7), CD56 (NCAM16), CD45 (HI30), CD69 (FN50), Alpha4Beta7 (NHP), CD103 (2G5), HLADR (L243), and CD45RA (HI100). Dead cells are excluded from analysis based on staining for LIVE/DEAD™ Near-IR Dead Cell Stain (Molecular Probes, Invitrogen Grand Island, NY). Fox-P3 and Ki-67 stains are performed after cells are stained for surface antigens, followed by permeabilization/fixation using the Invitrogen intracellular staining protocol kit and protocol, followed by intracellular staining for 30 min at RT. Samples are washed with FACS wash buffer and centrifuged at 1500 rotations per minute (RPM) for 5 min. The samples are acquired on a LSRFortessa™ (BD Biosciences, San Jose, CA), and a minimum of 500,000 total events are collected for each sample. Using FlowJo™ software version X.0.7 (Tree Star, Inc., Ashland, OR), data is analyzed after gating out dead cells, and subsequently gating on the CD45^+^ leukocytes population. CD3^+^ cell subsets are gated, and all analyses with CD4^+^ T-cells subsets are performed on parent CD4^+^ T-cell subsets.

We characterize subsets of CD4 + T cells expressing markers of activation (HLA-DR, CD69), cell trafficking (CD103, α4β7), cell regulation (Fox-P3), proliferation (Ki67), and tissue resident (CD69, CD103). Tissue-resident markers are characterized by the expression of CD103 and CD69 [59], which bind to E-cadherin expressed in tight junctions of epithelial cells in the mucosal surface [60], a homing marker expressed on T cells at mucosal sites. CCR7 regulates migration to lymph nodes [61]. α4β7 is a heterodimeric integrin receptor involved in T cell migration into the gut-associated lymphoid tissue, which has been associated with HIV acquisition in macaque models [61]. Ki67 is a prototypical cell cycle-related protein exclusively expressed on proliferating, not quiescent cells. CD3^+^CD4^+^ T cells are analyzed for co-expression of T cell activation, trafficking, and proliferation markers and reported as a percent of total lymphocytes and total CD4^+^ cells.

### Cytokines and immune-related protein assays

A panel of soluble markers including pro-inflammatory, anti-inflammatory, inhibitory, and chemotaxic cytokines and chemokines were selected based on their ability to be measured in plasma and CVL, their role in HIV or STI risk (e.g., RANTES, MIP-1B, IL8), or their ability to influence activation or recruitment of HIV target cells to the FGT (e.g., IL1, IP10) [62–64]. Using MSD multiplex immunoassays, we evaluate CVL supernatant and plasma samples collected at each study visit.

The following cytokines and immune-related proteins are quantified using U-PLEX Biomarker Group 1 Panel (Meso Scale Diagnostics, Rockville, MD, USA) according to the manufacturer's instructions: eotaxin, GM-CSF, IFN-α2a, IFN-γ, IL-1α, IL-1β, IL-2, IL-4, IL-5, IL-6, IL-8, IL-10, IL-12/IL-23p40, IL-17A, IP-10, MCP-1, MIP-1α, MIP-1β, TNF-α, TNF-β. RANTES are quantified using the R-PLEX Human RANTES Antibody Set (Meso Scale Discovery, Rockville, MD, USA), also according to the manufacturer's instructions. All assay standards and experimental samples are run in duplicate. The plates are read on the MSD QuickPlex instrument, and the concentrations are evaluated on the MSD software platform, which converts luminescence to protein concentrations based the respective calibrator concentrations. Duplicates that vary by > 20% are repeated. Concentrations below the lower limit of detection (LLOD) for a sample is imputed as the LLOD divided by the square root of 2.

### Ex vivo* HIV inhibitory activity in FGT secretions*

While direct ex vivo HIV challenge assays can be assessed, the variability in susceptibility of FGT tissue to HIV and the need for multiple biopsies, an invasive procedure, renders this an impractical strategy. An alternative approach is to measure the antimicrobial activity in CVL [65–71] which may represent a mixture of interactions mediated by secreted cytokines, chemokines, and antibodies along with molecules secreted by the microbiota [72, 73]. To evaluate the endogenous antimicrobial activity, CVL supernatant aliquots are stored at -80 °C on the same day of collection. Samples from visits 1, 2, 5, and 6 are shipped on dry ice to the lab of [name] at Albert Einstein School of Medicine for evaluation of FGT secretion inhibitory activity. To assess inhibitory activity against HIV, TZM-bl cells are infected with HIV-1BaL (~ 103 TCID50) mixed 1:1 with CVL or control buffer (normal saline containing 200 mg/mL bovine serum albumin) and infection monitored by assaying for luciferase activity 48 h after infection.

### Hormonal testing

Plasma samples are shipped to the Endocrine Technologies Core (ETC) at the Oregon National Primate Research Center (ONPRC) for sex steroid assays. Endogenous and exogenous hormones (estradiol, estrone, estriol, ethinyl estradiol, LNG, ENG, progesterone, MPA, norethindrone, testosterone, dehydroepiandrosterone, dihydrotestosterone, androstenedione, and dihydroprogesterone) are measured simultaneously by mass spectrometry using the method developed by Blue and colleagues [74]. Luteinizing hormone (LH) and follicle-stimulating hormone (FSH) concentrations are measured using a Roche Cobas e411 automatic immunoassay (Roche Diagnostics, Indianapolis, IN). These data enable us to confirm the phase of the cycle and other exogenous hormone exposure. At screening, participant self-report regarding prior HC use is considered acceptable for eligibility purposes. Plasma hormone levels are measured, as the results could affect eligibility of data inclusion.

### Specimen and data management

All study personnel have appropriate institution-specific laboratory and human subject safety trainings. Blood and secretion precautions are employed during phlebotomy, specimen collection, and specimen handling, as currently recommended by the Centers for Disease Control and Prevention. All infectious specimens are transported using packaging mandated in the Code of Federal Regulations, 42 CFR Part 72. Specimens (including the cervical biopsies) that are not used for research testing immediately are processed and stored for future testing. Plasma, PBMCs, vaginal swabs, anal swabs, and CVL supernatants are stored at -80 °C. Any remaining specimens are stored for potential future use only if the patient has consented to storage of specimens (a check box is included on the informed consent document). These specimens may be used in the future to further evaluate HIV, immunologic and/or microbiologic factors of interest, or as a source of DNA for future genetic analysis.

Study data are recorded on case report forms (CRFs) and entered into a HIPAA compliant web-based password-protected relational database (REDCap). Additional study data are housed in a HIPPA-compliant web-based password-protected One Drive database (Microsoft 365 Educational Licensing, Redmond, WA). All study paper forms and materials are maintained in locked cabinets and all data files are password protected in accordance with Emory IRB. Variables are continuously examined for data entry errors, inconsistencies, incompleteness, and plausibility of outliers with any changes documented.

### Data analysis

Univariate analyses will evaluate for differences in pre-contraception participant characteristics by HC method (DMPA, ENG-implant, LNG-IUD). If meaningful differences are observed, inverse propensity score weighting will be used to weight participants so that the study arms are more similar on pre-contraceptive participant characteristics. To account for repeated measures with a participant, all analyses will use mixed models with an appropriate distribution (normal, beta) and link function (identity, log), use an unstructured covariance matrix, and include a random effect for participant. For Aim 1, the primary outcome of interest is proportion of CCR5 expressing CD4^+^ T cells, while secondary outcomes are other immunologic outcomes from the flow cytometry and immune-related protein assays characteristics that may provide deeper insight into immune regulation in the FGT. Separate models for each outcome will contain time (categorical: visit 1, 2, 3, 4, 5, 6, 7, 8), contraceptive method (DMPA, ENG-implant, LNG-IUD), and a method by time interaction term. Models will additionally include important covariates such as age, race, STI presence, menstrual cycle characteristics and, if needed, incorporate propensity score weights. Model-based estimates of the change in mean outcome level within a contraceptive method over time (visit 1 and 2 versus each of 3, 6, and 12 months after contraceptive administration) will be computed. If the interaction term of method by time is significant, model-based comparisons of the means by contraceptive method and time (visit 1 and 2 versus each of: 3, 6, and 12 months after contraceptive administration) will also be computed pairwise for all possible combinations. Statistical significance will be set at α = 0.05 for the primary outcome of CCR5 and the main effects (contraceptive method, time) and the interaction term (method by time). Secondary outcomes will be evaluated for direction and magnitude of the associations. Models will be stratified by each specimen type (blood, CVL, cytobrush, biopsy).

In a subset of individuals, for a total of 75 women (25 per arm), cytobrush and blood specimens at visit 1, 2, 5 and 6 will be stained for more markers using BD symphony. In addition to T cells, we are also conducting innate cell marker analysis. These data include total, activated (express CD80 and CD86) and exhausted (expression of PD-L1) B cells, dendritic cells (myeloid DCs and plasmacytoid DCs), monocytes (classical, intermediate, and non-classical), macrophages, neutrophils and myeloid-derived suppressor cells (MDSCs including monocytic MDSCs and neutrophilic MDSCs). Principal component analysis will be applied in an exploratory analysis to characterize patterns of specific cell responses that may better describe activation, proliferation, differentiation, and maturation of immune cells in the FGT following HC use. Computational tools help us visualize relationships in high dimensional space and separate rare cells into populations based on distinct, multi-feature phenotypes. This methodology compares analysis of the human cell surface immunophenotyping dataset by three methods: Method 1: Bivariate gating analysis employs pairwise comparisons of markers to select, or gate, cell populations. Method 2: Visualization of t-Stochastic Neighbor Embedding (viSNE) analysis. This is a computational tool that projects cells onto a two-dimensional map such that the distances between cells in 2D reflect the distance between them in high-dimensional space. Method 3: Spanning-Tree Progression Analysis of Density-Normalized Events (SPADE) analysis. With high content single-cell experiments measuring > 30 features per cell, sequential bivariate gating can overlook populations of cells with low or unexpected patterns of markers expression. SPADE clusters cells based on phenotypic similarities in high-dimensional space and creates a minimum-spanning tree that illustrates the relationships between cell populations in two dimensions.

For Aim 2, we will evaluate alpha diversity at each time point, using the Shannon diversity index and Chao1 measures. We will also investigate microbiome CST over time. We will use additional statistical tools, such as a Principal Component Analysis to visualize clustering of the data based on distance metrics (weighted Unifrac, Bray–Curtis) [75] and advanced tools such as scree plots to identify the specific taxa that account for group differences. We will evaluate for effect modification on the microbial outcomes, such as BV status (BV presence or absence based on Nugent Score), species diversity, CST, and specific bacterial species by including interaction terms, separately and stratified by contraceptive method. An indicator for each outcome and an outcome by time interaction term will be added to the contraceptive method stratified mixed models. If the outcome by time interaction term is significant, model-based comparisons of the means by outcome and time (visit 1 and 2 versus each of: 3, 6, and 12 months after contraceptive administration) will also be computed pairwise for all possible combinations. As the primary independent variable of interest is BV, statistical significance will be set at α = 0.05 for the main effects (BV, time) and interaction term (BV by time) from the repeated measures analysis for CCR5 expression.

Analyses will be conducted using SAS software (SAS Institute, Cary, NC) and R (R Core Team).

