**Table 1 Tab1:** Comparative properties of three-progestin-only contraceptive methods used in this study

	**Depot Medroxyprogesterone Acetate (DMPA)**	**Levonorgestrel IUD**	**Etonogestrel Implant**
**Trade-name**	DepoProvera	Liletta	Nexplanon
**Progestin**	Medroxyprogesterone acetate (MPA) 1st generation	Levonorgestrel (LNG) 2nd generation	Etonogestrel (ENG) 3rd generation
**Delivery**	Intramuscular Injection	Intrauterine Device	Sub-dermal Implant
**Length of Use**	3 months	6 years	3 years
**Global Utilization**	High	Low	Low
**Ovulation Inhibition**	High	Low	High
**Endogenous estrogen inhibition**	Yes	No	Some initially

A significant difference between these methods is the kinetics of systemic progestin release with varying degrees of hypothalamic-pituitary-ovarian (HPO) axis modulation and differential estrogen suppression [8]. DMPA plasma concentrations peak in the week after administration, followed by a plateau of serum concentrations for about three months with suppression of endogenous estradiol and progesterone levels [10]. After a peak following ENG-implant insertion, concentrations reach steady-state levels at about 4–6 months and remain sufficient to prevent ovulation for three years. Ovarian activity slowly increases with estradiol levels in the normal range after six months; thus, serum estrogen concentrations are significantly higher in ENG-implant users compared to DMPA users [11]. A few weeks after placement of LNG-IUD, steady-state plasma LNG concentration is reached, and levels are maintained for at least five years after insertion. Ovulatory function is normal, and there are no changes in endogenous estradiol and progesterone concentrations [12]. Although systemic levels of LNG are low, the impact of higher hormone concentrations localized to the female genital tract (FGT) on immune function is unknown.

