### Power/sample size

For Aim 1, our pilot longitudinal study among women treated with DMPA, LNG-IUD, and ENG-implant provided estimates utilized in sample size calculation. The pilot study evaluated CVL CCR5 levels at four different time points (two visits pre-contraceptive, two visits post-contraceptive) with *n* = 148 total visits [76]. At the pre-contraceptive time point, 23.0% (SD 16.1) of CVL CD4^+^ T-cells expressed CCR5. Post-contraceptive, mean percent of CD4^+^ T-cells expressing CCR5 was 38.3, 34.1 and 23.6 for DMPA, ENG-implant and LNG-IUD, respectively, which represents a 66%, 48% and 3% increase above the pre-contraceptive measurement, respectively [77]. Given 75 women in each contraceptive method arm (DMPA, LNG-IUD, ENG-implant) and allowing for 20% attrition produces a final sample size of 60 women per arm. Assuming the smallest clinically- meaningful change in the percentage of CD4^+^ T cells expressing CCR5 level is 50% and that change will only be observed for DMPA and ENG-implant (not LNG-IUD), produces an effect size of 0.3 (effect SD 2.7). This design achieves 92% power to test the HC method (DMPA, ENG-implant, LNG-IUD) by time (pre-/post-contraceptive) interaction using a Geisser-Greenhouse Corrected F test when significance level is 0.05. Secondary outcomes will be evaluated for direction and magnitude of the associations.

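### The stated 92% power is for a 2-df method by pre/post interaction, but the planned Aim 1 test is a 14-df method by eight-visit interaction, which also gates the between-method comparisons

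*Protocol article*

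**What the plan says.** Power/sample size (Aim 1) describes the design as having 92% power "to test the HC method (DMPA, ENG-implant, LNG-IUD) by time (pre-/post-contraceptive) interaction using a Geisser-Greenhouse Corrected F test", with time at two levels, before and after contraception.

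Data analysis (Aim 1) fits a different time factor: "Separate models for each outcome will contain time (categorical: visit 1, 2, 3, 4, 5, 6, 7, 8". It adds "contraceptive method (DMPA, ENG-implant, LNG-IUD), and a method by time interaction term" and tests that term at 0.05 for CCR5. No pre/post or month-level contrast is named as the test.

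Two sets of estimates follow:
- "Model-based estimates of the change in mean outcome level within a contraceptive method over time" (visits 1 and 2 against 3, 6 and 12 months) are always computed.
- Comparisons between methods are conditional: "If the interaction term of method by time is significant, model-based comparisons of the means by contraceptive method and time" are computed in that case only.

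**The concern.** Three methods by two periods give (3−1)(2−1) = 2 df. Three methods by eight visits give (3−1)(8−1) = 14 df. These are different tests, so the power of one cannot be quoted for the other.

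The 14 df divide as follows:
- 2 df: the average pre/post change, compared between methods. This is what was powered.
- 4 df: differences among 3, 6 and 12 months, compared between methods.
- 8 df: differences within a visit pair (1 v 2, 3 v 4, 5 v 6, 7 v 8), compared between methods. Two of these 8 (visit 1 v 2) precede any contraceptive use and contrast the luteal with the follicular visit (Table 2).

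The omnibus term can therefore miss a pre/post difference that the 2-df contrast would find, and can be significant when no such difference exists.

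This matters because the term acts as a gate. How the effects differ by contraceptive type is part of the study's overarching hypothesis (Background). Those comparisons are shown only after a significant omnibus result, and estimates shown only after significance tend to be too large. The within-method before/after changes, which have no concurrent comparator, are reported in every case.

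**Working it through.** **Inputs.** Power/sample size, Aim 1: 60 women per arm after attrition; pre-contraceptive mean 23.0; a 50% rise (11.5 points) for DMPA and ENG-implant and none for LNG-IUD; effect size 0.3, effect SD 2.7; α = 0.05. Power/sample size, Aim 2, assumed to apply to Aim 1: SD 15.9 pre and 22.1 post, pre/post correlation 0.502. The correlation among visits within the same period is not given, so it is varied.

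**1. The plan's own figure.**
- Changes by arm are 11.5, 11.5 and 0, with mean 7.667. Their sum of squared deviations is 11.5² × 2/3 = 88.17, and 60 × 88.17 = 5290.
- Their SD is √(88.17/3) = 5.42. Half of this, 2.71, is the SD of the interaction effects (stated 2.7).
- Variance of one woman's change: 15.9² + 22.1² − 2 × 0.502 × 15.9 × 22.1 = 388.4, so the SD is 19.71.
- Effect size 5.42/19.71 = 0.275 (0.3 to one decimal). Noncentrality λ = 5290/388.4 = 13.6.
- Noncentral F on 2 and 177 df: power 91.6%.

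So the 92% is the 2-df test with one pre and one post value.

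**2. Both tests on all eight visits at the 50% effect.** Let w be the within-period correlation and keep the cross-period correlation at 0.502. The variance of (mean of visits 3–8 minus mean of visits 1–2) is

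15.9²(1+w)/2 + 22.1²(1+5w)/6 − 2 × 0.502 × 15.9 × 22.1.

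For w = 0.8 this is 227.5 + 407.0 − 352.8 = 281.7, so λ = 5290/281.7 = 18.8. In this structure λ is the same for both tests. Only the degrees of freedom differ: F(14, 340), the Hotelling-Lawley approximation, against F(2, 177).

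| w | λ | 14-df power | 2-df power |
|---|---|---|---|
| 0.502 | 43.1 | 99.7% | >99.9% |
| 0.6 | 30.2 | 96.5% | 99.9% |
| 0.7 | 23.2 | 88.9% | 99.3% |
| 0.8 | 18.8 | 79.5% | 97.7% |
| 0.9 | 15.8 | 70.1% | 95.1% |

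Simulation agreed at the three settings checked: 99.6% against 100% at w = 0.502, 79.5% against 98.2% at 0.8, and 68.7% against 94.8% at 0.9.

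**3. Significance without a pre/post difference.** Assume one arm swings by 6 points within each post pair (+3, then −3) and no method has a mean pre/post change. With all correlations 0.502 and post SD 22.1:

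λ = 60 × (2/3) × (6 × 3²) / (22.1² × 0.498) = 2160/243.2 = 8.9.

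The 14-df test then rejects 40% of the time. The 2-df contrast has λ = 0 and stays at 5%.

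If the same 6-point swing occurs only between visits 1 and 2, λ = 60 × (2/3) × (2 × 3²) / (15.9² × 0.498) = 720/125.9 = 5.7, and the test rejects 25% of the time. The swing sizes are illustrations; the article gives none.

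**The case against.** **Sizing on a collapsed design is common and can be conservative.** This stands in part. Two pre and six post visits carry more information than one of each. If all visits correlate at 0.502, the 14-df test has 99.7% power at the 50% change that the plan calls the smallest clinically meaningful. A reader might infer that the study is underpowered, or that the 92% was miscalculated. The documents support neither: the figure reproduces for the test it names, and 14-df power falls below 92% at 60 per arm only if within-period correlation is about 0.7 or more, which is not stated. Loss of participants also matters, since the Discussion reports early terminations and missed visits. Under the 0.502 correlation throughout, 14-df power is 95% at 40 per arm and 84% at 30.

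**Much of what the omnibus detects is of interest.** This stands. Differences among 3, 6 and 12 months belong to the study question. For DMPA, Table 2 places administration at visits 3, 5 and 7 but not at 4, 6 and 8, and the Background says "DMPA plasma concentrations peak in the week after administration". A reader might treat within-pair swings as unrelated to contraception, but a swing around re-injection would be a contraceptive effect. Only the visit 1 v 2 component precedes all exposure. What remains is narrower: a significant term need not mean that any method's pre/post change differs from another's.

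**Testing an interaction before pairwise follow-up is conventional, and the within-method changes allow method differences to be read off.** The convention is real, but reading off point estimates gives no interval for the difference between methods. The wording about all possible pairwise combinations might suggest a very large family of comparisons. The parenthetical limiting them to baseline against 3, 6 and 12 months supports nine: three method pairs by three times.

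**Conclusion.** The point holds as a mismatch between the test that is powered and the test that is planned, made worse by the gate. The 92% belongs to the 2-df method by pre/post interaction, not to the 14-df term in the Data analysis section.

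For a pre/post pattern the 14-df test was the weaker one in every setting tried. At the design effect the cost runs from nothing that matters (99.7% against more than 99.9%) to about 10, 18 or 25 percentage points at within-period correlations of 0.7, 0.8 or 0.9. These figures rest on the Aim 2 SDs and correlation carrying over to Aim 1, on 60 women per arm with complete visits, and on an equal change at every post visit. The 40% rejection rate without a pre/post difference rests in addition on an assumed swing.

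The structural facts need no assumption: 2 df against 14 df, 8 of the 14 within visit pairs, and between-method estimates conditional on the omnibus result. This should be changed, but it does not undermine the design.

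**What to change.** - Keep the eight-visit model.
- Name as the primary Aim 1 test the 2-df contrast between methods of (mean of visits 3–8 minus mean of visits 1–2), which matches the interaction that was powered.
- Report the nine between-method differences in change (three method pairs by 3, 6 and 12 months) with confidence intervals, whatever the omnibus result.
- State that 92% refers to the pre/post contrast, and restate the power for the visits actually used, giving the within-period correlation assumed.

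The cost is one contrast statement and some rewording, with no change to data collection. The small downside is that the primary test is less sensitive to time patterns that average out over follow-up; the nine contrasts still show differences between months.

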**Methods:**

CHIME is an observational cohort study where participants attend 2 visits prior to initiating the HC method of their choice, and then attend 6 visits over 12 months with biological sampling (vaginal swabs, cervicovaginal lavage, cytobrush and blood) for immunological, bacteriological, and virological analyses at each visit. Immune profiling will be evaluated by multi-color flow cytometry to determine how different T-cell subsets, in particular the CD4 T-cell subsets, change during the course of contraceptive use and whether they have different profiles in the FGT compared to the systemic compartment. The study aims are (1) to characterize the alterations in FGT and systemic immune profiles associated with three long-acting progestin-only HC and (2) to evaluate the vaginal microenvironment, determined by 16 s rRNA sequencing, as an individual-level risk factor and moderator of genital and systemic immune profile changes following exposure to three commonly used HC. Data collection started in March 2019 and is scheduled to be completed in October 2024.

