### Participant timeline

Upon successful screening and confirmation of eligibility, study staff schedule participants for study visit 1 approximately three weeks following the onset of their menses (luteal phase for women who cycle every 22–35 days). The timing for visit 1 and subsequent study visits will occur according to the schedule outlined in Table 2. At each visit, an interval assessment of bleeding and hormonal contraception use is collected and used to determine the phase of the menstrual cycle where applicable. Participants choose the specific contraceptive type that is initiated at visit 2. Laboratory personnel are blinded to contraceptive choice.

**Table 2 Tab2:** Participant timeline

	**Pre Contraception**			**Post Contraception**						
Study Activities	*Screen*	*Visit 1*	*Visit 2*	*Visit 3 & 4*		*Visit 5 & 6*		*Visit 6a*	*Visit 7 & 8*	
Timing of visit		*Luteal Phase*	*Follicular Phase*	*3 months*		*6 months*		*9 months*	*12 months*	
**Informed consent**	X									
**Complete history and physical exam (if indicated)**	X									
**Targeted history, questionnaire, and physical exam**		X	X	X	X	X	X		X	X
**RPR and HSV**		X								
**HIV Ora-Quick Test**	X					X			X	
**Pregnancy test**	X	X	X	X		X		X	X	
**DMPA administration**			X	X		X		X	X	
**ENG-implant or LNG-IUD placement**			X							
**Bleeding diary**			X	X						
**Genital/rectal sampling**^**a**^		X	X	X	X	X	X		X	X
**Blood sampling**^**b**^	X	X	X	X	X	X	X		X	X
**Cervical/Vaginal biopsies**^**c**^			X		X		X			X
**Flow-Cytometry**		X	X	X	X	X	X		X	X
**Cytokines & Immune-related proteins**		X	X	X	X	X	X		X	X
**HIV inhibitory activity**		X	X			X	X			

^a^Cervicovaginal lavage and cytobrush: immunologic testing, PSA; swabs: STIs, wet-mount, gram stain, microbiome, rectal microbiome; ^b^Blood: Immunologic testing, hormone panel ^c^Optional/only if subject consents

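### The primary CCR5 outcome has no named primary specimen or model term: three terms in four specimen models each get an unadjusted 0.05, including a confounded method main effect

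*Protocol article*

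**What the plan says.** All references are to the protocol article.

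- **Outcome (Data analysis).** For Aim 1, "the primary outcome of interest is proportion of CCR5 expressing" CD4+ T cells. No specimen, visit or contrast is attached to that definition.
- **Terms tested (Data analysis).** "Statistical significance will be set at α = 0.05 for the primary outcome of CCR5 and the main effects (contraceptive method, time"; the sentence continues "and the interaction term (method by time". No multiplicity adjustment or order of testing is given for these three terms. Pairwise method comparisons are made only if the interaction is significant; the main effects are not gated.
- **Specimens (Data analysis).** "Models will be stratified by each specimen type (blood, CVL, cytobrush, biopsy".
- **Time and method.** Each model "will contain time (categorical: visit 1, 2, 3, 4, 5, 6, 7, 8), contraceptive method" and their interaction. Table 2 places visits 1 and 2 before contraception. Under Participant timeline, "Participants choose the specific contraceptive type that is initiated at visit 2".
- **Sample size (Power/sample size).** "The pilot study evaluated CVL CCR5 levels at four different time points". From these data the article derives 92% power, with 60 women per arm, for the method by pre/post interaction. No other Aim 1 test is powered.

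**The concern.** There are two separate problems.

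**Which result is the primary one.** Three terms in four specimen models make 12 tests of the primary outcome, each at 0.05. The power section rests on one of them. A reader of the final report could not tell from the plan whether, say, a significant time effect in blood alone counts as the primary finding.

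**What the method main effect measures.** It averages over all eight visits, two of which precede any contraceptive use. Because women select their method, a stable difference in CCR5 between those who choose DMPA, the implant or the IUD enters this term in full. The interaction compares change from the pre-contraception visits, so a stable difference cancels. The plan gives both terms the same inferential status. Adjusting for multiplicity would not repair this, because it is a bias and not an excess of tests.

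**Working it through.** **1. The plan's own power figure.** Inputs from Power/sample size: pre-contraception mean 23.0, a 50% rise for DMPA and implant (to 34.5), none for the IUD, 60 per arm (180 in total).

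- Interaction effects are ±1.917 in two arms and ±3.833 in the third. Their root mean square is 2.71, against the stated 2.7.
- Power uses a noncentral F with 2 and 177 df and λ = 180 × f². With two time points the Geisser-Greenhouse correction has no effect.
- f = 0.30 exactly gives 95.6%; f = 0.277, which rounds to 0.3, gives 92.0%.
- The SD and correlation behind the Aim 1 effect size are not fully given. Borrowing the Aim 2 values (SDs 15.9 and 22.1, root mean square 19.25; correlation 0.502), the error SD is 19.25 × √(0.498/2) = 9.61, f = 2.71/9.61 = 0.282, and power is 93.0%.

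The stated 92% is therefore consistent with its inputs within rounding, and it belongs to a 2-df test. In the planned model, with eight visits as categories, the interaction has (3 − 1) × (8 − 1) = 14 df, so the powered test is not literally the one that the model delivers.

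**2. False-positive chance, if any significant test counted.** For independent tests this is 1 − 0.95^k.

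| Tests counted | k | Independent |
|---|---|---|
| Three terms, one specimen | 3 | 14.3% |
| Interaction, four specimens | 4 | 18.5% |
| All terms, all specimens | 12 | 46.0% |

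The specimens come from the same women, so their tests are correlated. A null simulation used 60 per arm, eight visits, within-woman correlation 0.502, and biopsy at visits 2, 4, 6 and 8 in an assumed half of the women. For all 12 tests it gave 45%, 44%, 42% and 33% at assumed cross-specimen correlations of 0, 0.3, 0.6 and 0.9. For the interaction in four specimens it gave 17%, 17%, 16% and 13%.

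**3. Method main effect with no contraceptive effect.** Assume one arm sits d points higher at every visit, with no covariates or weighting. Then λ = 60 × d² × (2/3) / V on 2 and 177 df, where V is the variance of a woman's eight-visit mean.

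- SD 16.1 at all visits, r = 0.502: V = 16.1² × (1/8 + 7/8 × 0.502) = 146.3.
- SD 15.9 at two visits and 22.1 at six, r = 0.502: V = 238.7.

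| Assumed shift d | SD 16.1 | SD 15.9/22.1 |
|---|---|---|
| 2 points | 14% | 10% |
| 4 points | 44% | 29% |
| 6 points | 80% | 58% |

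In the simulation with SD 16.1, the CVL interaction was significant in about 5-6% of studies whatever the shift.

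**The case against.** - **No success rule is stated.** Nothing in the article says that any one of the 12 tests makes the primary result positive. A reader might infer that the study's type I error is 46%. The documents do not support that: the figure needs an any-of-12 rule and independent tests. This stands, and the figures are upper values for one possible reading.
- **A lead test is implied.** Only the interaction is powered, with CVL pilot data, and pairwise comparisons depend on it. This also stands, and it makes the repair easy. But the analysis section still grants 0.05 to the other terms and specimens.
- **Confounding is addressed.** Covariates are planned, with inverse propensity weighting if the arms differ, and the Discussion lists further variables. The percentages for the method main effect leave all of this out, and no baseline difference between choosers is reported. A reader might take 80% as the expected rate of spurious method effects; it is the result of one assumed shift with the smaller SD and no adjustment. Adjustment may reduce the bias, but weighting is conditional and neither section names pre-contraception CCR5 among the adjustment variables.
- **Exploratory cohort.** The Discussion calls the study exploratory, and strict familywise control is not a universal requirement for such work. That lowers the severity. The plan nevertheless reserves a significance threshold for the primary outcome and reads secondary outcomes by direction and magnitude only, so the primary test should be identifiable.
- **Compartments.** The abstract speaks of asking "whether they have different profiles in the FGT compared to the systemic compartment", and a reader might infer that separate specimen models leave a planned test undone. The numbered aims and objectives state no between-compartment test, so that criticism is not made here.

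**Conclusion.** The point holds as a flaw in a stated rule that wording can repair, short of a fault that invalidates the design. The plan sets an unadjusted 0.05 for three terms in four specimen models and names none as primary, while the sample size rests on one CVL interaction.

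Read loosely, the chance of at least one false-positive primary result is about 14% (three terms, one specimen), up to 18.5% (interaction, four specimens) or 33-46% (all 12), depending on cross-specimen correlation, which is assumed.

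The weightier part is the method main effect. Under assumed, unadjusted shifts of 4 or 6 points between choosers, it would be significant in 29-44% or 58-80% of studies without any contraceptive effect, and in fewer to the extent that the planned adjustment works. It should not carry a claim of contraceptive effect.

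**What to change.** In Data analysis, name the method by period (pre versus post) interaction for CVL CCR5 as the single primary test at α = 0.05. This is the test that the power section describes, so the stated 92% is kept. Splitting 0.05 equally would cost power: about 81% over four specimens (0.0125 each) and about 69% over all 12 tests (0.0042 each), starting from 92%.

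State that no contraceptive effect will be claimed from the significance of the method main effect. Treat the time main effect and the blood, cytobrush and biopsy models as supportive, reported as estimates with intervals, or with Holm adjustment across specimens if p-values are wanted.

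The cost is a few sentences and no new data. The downside is that blood, cytobrush and biopsy lose primary status.
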